## Abstract

**Background:**

Knee osteoarthritis (OA) is a leading cause of global disability. According to current guidelines, exercise is the most recommended and important non-surgical treatment for knee OA. However, the best type of exercise for this condition remains unclear. Evidence has shown that traditional Chinese exercises may be more effective. Therefore, the current prospective, two-armed, single-center randomized controlled trial (RCT) aimed to identify an effective physiotherapy for knee OA.

**Methods/design:**

In total, 114 patients with painful knee OA will be recruited from the orthopedic outpatient department of Shanghai Jiao Tong University Affiliated Sixth People’s Hospital. To compare the therapeutic effect of two different home-based exercise programs, the participants will be randomly assigned into the experimental group (leg swing exercise) or the control group (quadriceps strengthening exercise). Each participant in both groups will be required to attend five individual sessions with a physiotherapist who will teach the exercise program and monitor progress. Participants will be instructed to perform the exercises at home every day for 12 weeks. Clinical outcomes will be assessed at baseline and 12 and 24 weeks after starting the intervention. The primary outcomes are average overall knee pain and physical function in daily life. The secondary outcomes include other measures of knee pain, physical function, patient-perceived satisfactory improvement, health-related quality of life, physical activity and performance, muscle strength of the lower limb, and adherence.

**Discussion:**

This study will provide more evidence on the effects of traditional Chinese exercise on improving physical function and relieving joint pain among patients with knee OA. If proven effective, leg swing exercise can be used as a non-surgical treatment for knee OA in the future.

**Trial registration:**

Chinese Clinical Trial Registry ChiCTR2000039005. Registered on 13 October 2020.

**Supplementary Information:**

The online version contains supplementary material available at 10.1186/s13063-022-06282-0.

## Background

Knee osteoarthritis (OA) is a leading cause of global disability [1, 2]. In 2017, the global prevalence of hip and knee OA was approximately 303.1 million cases, and the age-standardized prevalence was 3754.2 per 100,000 [2]. Patients with OA may present with increasing joint pain, worsening physical function, decreased physical activity, and low quality of life [3]. Thus, numerous patients with hip and knee OA require joint replacement surgery, and the economic burden to the society worldwide has been significant [4]. With the aging of the global population and the increasing incidence of obesity, OA can become a serious public health issue.

Currently, there is no definitive treatment for knee OA and effective therapy options are limited [5]. Better treatments are thus needed to relieve OA symptoms and improve physical function while minimizing the economic burden to both patients and the global society [6].

Thus far, exercise is one of the most recommended non-surgical treatments for knee OA regardless of age, disease severity, and comorbidities [5, 6]. Clinical guideline for treating knee OA recommend several types of exercise. These include aquatic exercises, mind-body exercises, and structured land-based exercises such as strength training [6]. Previous studies have found that these non-surgical treatments can relieve pain, improve physical function, enhance quality of life, and delay disease progression to varying degrees [5, 7]. Considering the safety and economic efficiency of exercise for patients with knee OA, lower limb muscle strengthening exercise has become an important part of routine treatment.

In terms of mind-body exercise, traditional Chinese exercises such as T’ai chi and Baduanjin have been shown to have some effects in controlling pain and improving physical function among patients with knee OA [7–10]. Both exercises are a combination of muscle strengthening and aerobic training. However, considering that T’ai chi and Baduanjin are comprehensive whole-body exercises, elderly individuals may find these exercises time-consuming and cognitively demanding. Therefore, a simple exercise program focusing on the comprehensive treatment of the lower limb is required.

In fact, there is another type of traditional Chinese exercise referred to as Daoyin, which is easier and is less cognitively demanding [11]. Although each of these exercises has its own training characteristics, they have common features. In general, Daoyin integrates both static and dynamic exercises with a great emphasis on regulating, breathing, and exercising intrinsic control and mental intent [12].

This study focused on leg swing exercise, which is an extremely important part of Daoyin based on the traditional Chinese medicine theory. This exercise is selected and recommended for three reasons. First, compared with T’ai chi and Baduanjin, the leg swing exercise of Daoyin focuses more on comprehensive training of the lower limb. This exercise is a combination of elements including strength training, active range of motion exercise, and aerobic activity. Second, since patients with knee OA have lower isokinetic strength in the hip muscles than healthy people, strengthening the muscles surrounding the hip joint may decrease pain [13, 14]. Leg swing exercise focuses on the joints of the lower limb including hip and knee joints. Third, as this clinical study will include mostly elderly participants, the exercise program should be simple enough for them to learn so that adherence will be good.

This clinical study aims to identify whether leg swing exercise, which is a type of Chinese traditional exercise, can relieve pain and improve physical function among patients with knee OA. Moreover, it wants to compare the efficacy of two different exercise programs on different outcomes such as knee pain, physical performance, health-related quality of life, patient-perceived satisfactory improvement, and lower limb muscle strength. We hypothesized that participants who take leg swing exercise will have greater improvements in pain intensity and physical function than those who take quadriceps strengthening exercise at 12 and 24 weeks after starting the intervention.

## Methods/design

### Study design

This protocol is designed according to the Standard Protocol Items: Recommendations for Interventional Trials (SPIRIT) guidelines for clinical trials [15] (see Additional file 1) and the Osteoarthritis Research Society International (OARSI) Clinical Trials recommendations for rehabilitation interventions [16]. To the best of our knowledge, previous studies investigated the effects of muscle strengthening exercise in patients with knee OA, focusing mainly on the quadriceps [17]. Leg swing exercise is a novel rehabilitation treatment for knee OA. Meanwhile, the quadriceps strengthening exercise is the established intervention that can validate the efficacy of leg swing exercise [16]. This study will be a prospective, two-armed, single-center randomized controlled trial (RCT) in which participants with painful knee OA will be randomly assigned into the experimental group (leg swing exercise) or the control group (quadriceps strengthening exercise). Figure 1 shows the RCT procedure. The 2–3 year trial will be conducted at Shanghai Jiao Tong University Affiliated Sixth People’s Hospital. Clinical assessments will be performed at baseline and 12 and 24 weeks after starting the intervention. Assessment outcomes will be analyzed in randomization groups. The trial was registered with the Chinese Clinical Trial Registry (ChiCTR2000039005) on October 13, 2020. This study has been approved by the Human Research Ethics Committee of Shanghai Sixth People’s Hospital prior to recruitment, and all participants will provide informed consent.

**Fig. 1 Fig1:**
[figure not shown]
Flow diagram of the RCT

### Participants

In total, 114 patients aged ≥ 50 years with painful knee OA will be recruited from the orthopedic outpatient department of Shanghai Jiao Tong University Affiliated Sixth People’s Hospital.

The inclusion criteria will be as follows:
Patients aged ≥ 50 years oldThose with OA in at least one knee according to the American College of Rheumatology Classification Criteria [18]Those with knee pain on most days of the last monthThose presenting with knee pain for at least 3 monthsThose reporting a minimum average overall knee pain intensity of 40 on a 100-mm visual analog score (VAS) for most days in the last month [19]Those with a Kellgren-Lawrence grade (K-L grade) of 2–4 for knee OAThose willing to follow the physiotherapist’s recommendation for exercise trainingThose with smartphones downloaded with the WeChat app who are willing to receive text message reminders and send feedback to the physiotherapist during the trial.

Knee OA will be further confirmed via physical examinations in the orthopedic outpatient department and a full-length lower limb radiography will be performed in the hospital.

The exclusion criteria will be as follows:
Patients with knee joint injection within the last 6 months or planned surgery in the next 12 monthsThose who have taken oral corticosteroids within the last month or who received intra-articular corticosteroid injection within the last 3 monthsThose with systemic arthritic conditionsThose with previous knee fracture or malignancyThose with a previous history of hip or knee joint replacement, tibial osteotomy, or other surgeries of the hip or knee jointThose with any other neurological, muscular, or joint diseases that may currently affect the physical function of the lower limbThose who have participated in hip or knee muscle strengthening programs within the last 3 monthsThose without independent mobilityThose who reject the leg swing exercise or those who do not provide informed consent.

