### Randomization allocation concealment

Patients will be recruited in strict accordance with the inclusion and exclusion criteria and will be subsequently randomized into the experimental group (leg swing exercise) or the control group (quadriceps strengthening exercise) at a ratio of 1:1. Specifically, an independent researcher who is not a part of the trial will generate 114 unique seven-digit codes using the random number function in the SAS software version 9.4 (SAS Institute Inc., Cary, NC, USA). Then these codes will be randomized into two groups and will be placed in a sealed, sequentially numbered, opaque envelope [22]. The envelopes will be stored securely. The recruited participants will be assigned to either the experimental or control group by extracting codes from the envelopes.

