### Blinding

Considering that most participants may have learned before the clinical trial that quadriceps strengthening exercise is a treatment for knee OA and that the group allocation can be revealed based on the interventional exercises, the participants will not be blinded to the treatment [16]. However, they will be blinded to the study hypotheses. As questionnaire-based outcomes are self-reported and participants are not blinded to treatments, the assessors of questionnaires will not be blinded. Since the physical performance tests are held in other enclosed rooms, assessors who collect physical function outcomes will be blinded. Statisticians who perform statistical analyses will be blinded. If there will be any unexpected adverse event caused by the exercise program, randomization allocation can be immediately unblinded by the study oversight committee.

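### The last exclusion criterion screens out refusal of the experimental exercise only; it should cover unwillingness to do either exercise

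*Protocol article*

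**What the plan says.** The protocol article, under Participants, closes its exclusion list with those "who reject the leg swing exercise or those who do not provide informed consent". The list has no counterpart for patients who reject the control exercise, a weighted straight leg raise.

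Two other provisions bear on willingness and apply to both arms. One inclusion criterion asks that patients be willing to do as the physiotherapist advises about exercise. Study design states that "all participants will provide informed consent".

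Eligibility comes before allocation: "Patients will be recruited in strict accordance with the inclusion and exclusion criteria and will be subsequently randomized into the experimental group" or the control group, "at a ratio of 1:1" (Randomization allocation concealment).

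Under Blinding, "the participants will not be blinded to the treatment", although "they will be blinded to the study hypotheses". Both primary outcomes, VAS pain and WOMAC physical function, are self-reported. The Background hypothesis is directional: "participants who take leg swing exercise will have greater improvements in pain intensity and physical function than those who take quadriceps strengthening exercise".

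**The concern.** An arm-specific refusal criterion applied before randomisation does not unbalance the arms at baseline. People averse to the control exercise are split evenly between the arms. The consequences of that aversion are not split evenly. Only those allocated to control are asked to do the exercise they dislike. The mirror-image group, people with a declared aversion to leg swing, has been removed at screening.

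A participant who dislikes the allocated exercise may do less of it, withdraw, or rate pain and function less favourably. In a trial unblinded to participants with self-reported primary outcomes, nothing in the measurement shields the comparison from this. Any net effect would tend to run in the direction of the trial's own hypothesis, so a critic could raise it against a positive result.

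Aversion to the control exercise is not far-fetched on the document's own description. The Control group section prescribes 10 repetitions in 10 sets, twice a day, which is 10 × 10 × 2 = 200 repetitions. Each is held for 10 s and lowered over about 3 s, so holding and lowering alone take 200 × 13 s = 2,600 s, or about 43 minutes a day, at an effort rated hard to very hard. Leg swing is demanding too, at about 1,000 swings a day. A reason for asking about acceptance of one exercise applies to the other.

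**Working it through.** **Reading the criteria together**

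- Open refusal of leg swing at screening: excluded by name.
- Open refusal of the quadriceps exercise at screening: not excluded by name. It can be caught by the general willingness criterion or by withheld consent, if the screener applies them that way.
- Reluctance that is not an open refusal: the document prompts the screener to ask about leg swing and gives no equivalent prompt for the control exercise.
- Reluctance that appears after allocation: possible in both arms, and no screening rule prevents it.

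The asymmetry therefore lies in what is explicitly screened, and the general criteria narrow it by an unknown amount.

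**Figures from the document (Sample size calculation)**

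- Target differences: 18 mm on the VAS, 6 WOMAC units.
- SDs of change: 30 mm and 12 units.
- 51 per group before dropout, 10% dropout, 57 per group recruited. Check: 51 / 0.90 = 56.7, rounded up to 57, and 2 × 57 = 114. The dropout allowance is 57 − 51 = 6 per arm.
- The 51 matches a one-sided t-test at effect size 0.5. A two-sided test would need 63 to 64. That is a separate matter, and this point does not depend on it.

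**Illustration of size**

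The document gives neither the share of participants averse to the control exercise nor the effect of that aversion. Both ranges below are assumptions.

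Let *f* be the share of enrolled participants still averse to the control exercise after screening and consent, and *m* the worsening in each such participant allocated to control. With 1:1 allocation:

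- Number affected in the control arm = *f* × 57: at 5%, 2.9; at 10%, 5.7; at 20%, 11.4.
- Shift in the between-arm difference = *f* × *m*.
  - VAS, lowest: 0.05 × 10 = 0.5 mm.
  - VAS, highest: 0.20 × 18 = 3.6 mm.
  - WOMAC with *m* = 6 units: 0.05 × 6 = 0.3; 0.10 × 6 = 0.6; 0.20 × 6 = 1.2 units.

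Standard error of the between-arm difference with 51 per arm = SD × √(2/51):

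- VAS: 30 × 0.198 = 5.9 mm. The shift is 0.5/5.9 ≈ 0.1 to 3.6/5.9 ≈ 0.6 standard errors.
- WOMAC: 12 × 0.198 = 2.4 units. The shift is 0.3/2.4 ≈ 0.1 to 1.2/2.4 = 0.5 standard errors.

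If the affected participants withdrew instead, then at 10% their number (5.7) would about equal the control arm's allowance of 6. Withdrawal and worse reporting are alternative routes for the same people, so the two figures must not be added.

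**The case against.** A reader might infer that every unwilling participant must end up in the control arm and none in the leg swing arm. The document does not support that. A candidate who openly refuses straight leg raises does not meet the general willingness criterion and can be excluded on it. Unwillingness to do leg swing can also emerge after allocation. The Experimental group section itself foresees participants who find prolonged standing on one leg difficult.

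A reader might also argue that the leg swing clause proves the general criteria insufficient, since otherwise it would be redundant. That inference is weak, because the list overlaps elsewhere. The six-month knee injection exclusion already covers a knee corticosteroid injection within three months, and lack of consent is listed although consent is required of everyone. Leg swing is described as novel, which is a plausible reason for naming it.

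On direction, Blinding notes that most participants may already know quadriceps strengthening as a treatment for knee OA. That familiarity could make aversion to control uncommon, or raise expectations of it, and so work against the suggested bias.

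It is tempting to add that the criterion reveals the hypothesis to participants. The article gives a list of criteria and no screening script, so nothing shows that candidates are asked about leg swing alone. Knowing which exercise is newer also does not disclose that it is expected to be superior.

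Finally, adherence is measured by several methods and causes of poor adherence are to be analysed, so some of the consequences would be visible.

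These arguments limit the claim and make a small effect likely. They leave the wording one-sided, and they do not show that the general criteria are applied as an equivalent screen for the control exercise.

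**Conclusion.** The point stands as a drafting asymmetry with a possible, probably small, bias. Known aversion is explicitly screened out for the experimental arm only. The willingness criterion and consent reduce the imbalance without clearly removing it. Baseline comparability is unaffected.

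Any residual effect would tend to favour leg swing, on the assumption that participants averse to the control exercise adhere less, withdraw more or report worse when allocated to it. Its size cannot be derived from the document. Under the assumed ranges it is 0.5 to 3.6 mm on the VAS and 0.3 to 1.2 WOMAC units, against targets of 18 mm and 6 units and below one standard error in each case. The case for acting is that the direction coincides with the hypothesis and the correction is cheap. It is not that the result is likely to be overturned.

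**What to change.** Replace the clause with a symmetric criterion: those unwilling to perform either of the two exercise programs if allocated to it. Ask it before the envelope is opened, in neutral wording that names both exercises and does not say which is experimental. Keep lack of consent as its own item.

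For participants already enrolled under the present criterion, report by arm the refusals of the allocated exercise, the withdrawals with reasons, and non-adherence. Much of the remaining value lies here. The protocol version is dated 6 March 2022 and recruitment was expected to end on 30 April 2022, about eight weeks later, so an eligibility amendment would reach few participants.

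The cost is one sentence in the eligibility list and the screening form, by amendment, and possibly a few more screening refusals. The reporting draws largely on adherence and attendance data that the trial already plans to collect.

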### Procedures

Eligible patients with knee OA who visit the orthopedic outpatient department of Shanghai Jiao Tong University Affiliated Sixth People’s Hospital will be identified. Primarily, the orthopedic doctor will assess the patient’s eligibility via physical examinations. Then the results of standing full-length radiography conducted within the last 6 months will be screened by an orthopedic doctor. If participants did not undergo radiography, the procedure will be performed in the hospital. After eligibility assessment and the collection of informed consent, the doctor will arrange for a meeting with the treating physiotherapist.

For participants with bilateral symptoms, both knees will be the subjects of rehabilitation. However, only the most symptomatic eligible knee (as identified according to K-L grade and pain intensity) will be selected for assessment. In cases in which bilateral knees are equally symptomatic, the right knee will be nominated.

Participants will visit the same physiotherapist five times (study weeks 1, 3, 6, 9, and 12) over the 12-week intervention and one time 12 weeks after the end of the intervention (study week 24). Baseline and follow-up assessments will be completed at the orthopedic outpatient department of Shanghai Sixth People’s Hospital. At other times, participants will be required to maintain contact with the physiotherapist. Considering that WeChat is the most common mobile social application in China and it can be easily used by elderly individuals, regular text message reminders will be sent by the physiotherapist via this application to help improve adherence. In addition, the physiotherapist can screen participants via video calls through WeChat if necessary.

During each visit, the physiotherapist will assess the adherence of participants and the progression of the home exercise program. Moreover, they will adjust the exercise program according to each participant’s progress and physical condition using the modified Borg Rating of Perceived Exertion (RPE) CR-10 scale [20, 21]. Each individual session will last about one hour. If participants show poor adherence, the causes will be analyzed in the final statistics. Clinical outcomes such as self-reported questionnaire results, physical performance, lower limb muscle strength, and adherence will be assessed 12 and 24 weeks after starting the intervention.

### Data collection and management

Case report forms will be created by the physiotherapist to collect all data obtained via paper-based questionnaires and physical performance tests in the orthopedic outpatient department. The text messages and video records will be stored electronically by the treating physiotherapist. All data will then be transferred and stored in secure electronic databases. Only the statisticians that perform the statistical analyses will have access to the database during the final analysis.

### Randomization allocation concealment

Patients will be recruited in strict accordance with the inclusion and exclusion criteria and will be subsequently randomized into the experimental group (leg swing exercise) or the control group (quadriceps strengthening exercise) at a ratio of 1:1. Specifically, an independent researcher who is not a part of the trial will generate 114 unique seven-digit codes using the random number function in the SAS software version 9.4 (SAS Institute Inc., Cary, NC, USA). Then these codes will be randomized into two groups and will be placed in a sealed, sequentially numbered, opaque envelope [22]. The envelopes will be stored securely. The recruited participants will be assigned to either the experimental or control group by extracting codes from the envelopes.

